### Acupuncture treatment

For every treatment visit, participants are treated with two acupuncture points [Baihui (GV20)] and [Shenting (GV24)]. Patients will be treated by an experienced acupuncturist with a working experience of at least 2 years in neurological rehabilitation with acupuncture. The targeted acupoints are described in detail in Table 3.

**Table 3 Tab3:** Acupuncture points selected in this protocol

Acupuncture points	Location
Baihui (GV20)	On the head, 5 ^*^B-cun superior to the anterior hairline, on the anterior median line
	Note 1: GV20 is located in the depression 1 ^*^B-cun anterior to the midpoint of the line from the anterior hairline to the posterior hairline
	Note 2: when the ears are folded, GV20 is located at the midpoint of the connecting line between the auricular apices
Shenting (GV24)	On the head, 0.5 ^*^B-cun superior to the anterior hairline, on the anterior median line.

^*^B-cun: proportional bone cun. This method divides the height of the human body into 75 equal units. Using joints on the surface of the body as the primary landmarks, the length and width of every body part is measured by such proportions

Before treatments, the targeted acupoints are sterilised with alcohol. While one hand fixates the target position, the other hand is used to insert the needle (Huatuo, single use, φ0.35 × 40 mm, distributor Suzhou HuaTuo Medical Instruments, Suzhou, China). The angle of insertion is approximately 10°–20° (between needle and scalp), the needle should be inserted to a depth of approximately 0.3–0.5 cun (1 cun = 3.33 cm). Following insertion, a 1-minute stimulation of the acupuncture point will be performed using bidirectional rotation of the needle’s sleeve. This provokes a sensation known as Deqi, which is commonly described as a ‘glowing’ feeling. The needle will be kept in this position for 30 minutes. The described manipulation will be repeated every 10 minutes and the needles are withdrawn after the fourth manipulation.

### Computer-assisted cognitive training with RehaCom

It is important to note that the CaCT group will use RehaCom (Hasomed Inc., Magdeburg, Germany, http://www.hasomed.de) in our study. Three rehabilitation centres from different countries will be involved in our study. Traditional cognitive training programs are delivered in individual or group format by a trained instructor, and differ primarily with regards to trained abilities, length and frequency of training, and specific strategies practiced [22]. Therefore, it is better to use a computer-assisted training program to ensure patients from different centres will all receive equal treatments. RehaCom has been translated into different languages and extensively used in cognitive rehabilitation following the relevant diseases, for example, stroke [23], schizophrenia and multiple sclerosis [24, 25].

The software has five different therapeutic programs aimed at restoration of attention, memory, executive functions, or visual field. Each program has one to four different tasks to choose from for each therapy session.

For the purpose of this study, three submodalities of attention will be targeted with CaCT: intensity, selectivity, and divided attention [26]. To approach intensity of attention, the RehaCom task called “Attention and Concentration” and “Vigilance” will be used. For selectivity the RehaCom task called “Alertness” for reaction behaviour and reactivity will be used. Divided attention will use the task called “Divided Attention Training 1 and 2”. Each task will start at the lowest difficulty level to allow progression according to the patient’s abilities. Only “Attention and Concentration” and “Divided Attention Training 2” will begin with level 4 and 2 respectively. A detailed description of the tasks and their content can be found on the developer’s site (Hasomed GmbH, www.hasomed.de).

### ACoTrain: acupuncture and computer-assisted attention training

For the combined group, patients will receive AP and CaCT combined, i.e. the CaCT will be performed while the needles are inserted.

### Outcome assessment

Outcomes will be measured once before intervention (T0) and once after intervention (T1, at 4 weeks) in a 1- to 1.5-hour assessment. Assessments will be conducted by a trained and experienced therapist or neuropsychologist blinded to group allocation. None of the assessors will participate in the treatment. The study will use a number of standardised scales to assess functional changes. At baseline, additional assessment of basic cognitive functioning will be administered for classification of the included patients.

### Primary outcome measure

#### Test for Attentional Performance (TAP)

The Test for Attentional Performance (TAP) is a computer-assisted standardised neuropsychological test [27] used to evaluate attention deficits. The procedures included in the test battery are: Alertness and Go/No Go for basic attention and general anticipation, incompatibility for divided visual-spatial attention, and divided attention. Outcomes are measured in reaction time (ms) and reported as percentile ranks. The TAP test has previously been shown to be both reliable and valid [28, 29]. Alertness is required for effective behaviour and deemed the basis of every attention performance. It is tested under two conditions measuring reactions times.React to a randomly appearing cross on the screen (click a button)React to a critical stimulus preceded by a cue stimulus presented as warning toneGo/No-Go task tests the ability to suppress an inappropriate reaction (control of impulsive behaviour). This is achieved by measuring the amount of correct reaction to the target stimuli. Five different patterns of a square are presented, only two are correctIncompatibility, a right- or left-pointing arrow appears on the left or right side of the screen. The patients are instructed to indicate the direction of the arrow, not the location of the arrowDivided attention assesses the capacity to pay attention to simultaneously ongoing processes. The test presents a visual and an auditory task, which must be processed in parallel (dual task)

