## Abstract

**Background:**

A majority of stroke survivors present with cognitive impairments. Attention disturbance, which leads to impaired concentration and overall reduced cognitive functions, is strongly associated with stroke. The clinical efficacy of acupuncture with Baihui (GV20) and Shenting (GV24) as well as computer-assisted cognitive training in stroke and post-stroke cognitive impairment have both been demonstrated in previous studies. To date, no systematic comparison of these exists and the potential beneficial effects of a combined application are yet to be examined. The main objective of this pilot study is to evaluate the effects of computer-assisted cognitive training compared to acupuncture on the outcomes of attention assessments. The second objective is to test the effects of a combined cognitive intervention that incorporates computer-assisted cognitive training and acupuncture (ACoTrain).

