### Interventions

All study interventions are described in Table 2 using the Template for Intervention Description and Replication checklist and guide, known as TIDieR. Patients will be evenly allocated to CaCT, AP, or ACT. All groups will additionally receive conventional neurorehabilitative treatment as prescribed by each clinic. The experimental intervention of this trial will be added to the existing therapy plan as a daily treatment of 30 minutes for 4 weeks (Monday to Friday). Every treatment will be documented on the therapy documentation sheet (standardised for each trial centre).

**Table 2 Tab2:** Description of study interventions based on the TIDieR template^*a^

Item	Computer-assisted cognitive training	Acupuncture	ACoTrain
1 Short name	Ca CT	AP	ACT
2 Why	Main objective is to evaluate the effects of computer-assisted cognitive training CaCT compared to AP on the outcomes of attention assessments		
	Second objective is to test the effects of a combined cognitive intervention that incorporates CaCT and AP		
3 What: materials	Ca CT (RehaCom, Hasomed Inc., Germany, http://www.hasomed.de) will be conducted in the study. Patients will sit in front of the RehaCom system. The training program will be displayed on the computer screen and they also can hear the sound feedback from the audio system. According to different training programs, patients will press a special RehaCom keyboard with large buttons to react	Acupuncture needle, which is single use, φ 0.35 × 40 mm, will be used for acupuncture treatment. The angle of insertion is approximately 10°–20° (between needle and scalp), the needle should be inserted to a depth of approximately 0.3–0.5B-cun	For the combined group, patients will receive AP and CaCT combined, i.e. the CaCT will be performed while the needles are inserted

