## Discussion

Cognitive impairments, such as, memory, executive function, and attention deficit frequently occur in stroke patients, though sometimes, attentional deficit is the only cognitive impairment apparent [40]. Sustaining attention is a prerequisite of motor relearning [41], which is essentially the mechanism of functional recovery after stroke [42]. The traditional neurocognitive strategies [43] used to improve attention deficit after stroke often result in incomplete resolution, and thus, more effective adjuvant strategies are needed.

Acupuncture focuses on the global cognitive function from the holistic conception of TCM, while the RehaCom cognitive training concerns the specific impaired cognitive functions, which need to be trained from the viewpoint of symptomatic treatment. However, the cognitive impairment after stroke is so complex that it needs an integrated method.

The aims of our study are to compare CaCT and AP efficacy in terms of attention improvement after stroke and to investigate the potential effect of a combination of both (ACT). The participants will have the study treatment added to their existing rehabilitation program and will be assessed for changes in attention (intensity, selectivity, and divided attention) at 4 weeks.

Although CaCT and AP both have shown to have beneficial effects on overall cognition in various studies, they have not been compared directly and for specific attentional performance. This is the first study of its kind that assesses attention-specific outcomes for both methods and not only compares the methods but also advances into new approaches where two methods well accepted in two very different cultures are combined to complement one another. The multicentric approach allows more generalisable interpretation [44] of the results and the usage of standardised and cross-culturally adapted assessments allows comparison and pooling of all study data coming from different trial centres.

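### A CaCT or ACT advantage over AP on the TAP may partly reflect task and device practice, and Go/No-Go as described is not scored on the suppression it is meant to test

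*Protocol article*

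**What the plan says.** The Abstract of the protocol article makes CaCT versus AP, judged on attention tests, the main comparison. The primary outcome section says that "The Test for Attentional Performance (TAP) is a computer-assisted standardised neuropsychological test" and lists its procedures as "Alertness and Go/No Go for basic attention and general anticipation, incompatibility for divided visual-spatial attention, and divided attention". On scale it says: "Outcomes are measured in reaction time (ms) and reported as percentile ranks". Alertness is described as clicking a button in response to a cross on the screen.

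On the treatment side, Table 2 (item 3) says that in CaCT "patients will press a special RehaCom keyboard with large buttons to react". Table 2 (item 4) and the RehaCom section name the modules: Attention and Concentration, Vigilance, Alertness ("for reaction behaviour and reactivity will be used"), and Divided Attention Training 1 and 2. The ACoTrain section gives the ACT arm the same training while the needles are in place. Table 2 (item 8) sets 20 sessions of 30 minutes in every arm.

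For Go/No-Go, the primary outcome section states the aim as control of impulsive reactions and then describes the measurement: "This is achieved by measuring the amount of correct reaction to the target stimuli". Five patterns are shown, of which two are targets.

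The Discussion says that participants "will be assessed for changes in attention (intensity, selectivity, and divided attention) at 4 weeks".

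**The concern.** Two of the three arms are trained in the medium, and with the type of response, in which the primary outcome is measured. Two TAP subtests also share their names with trained modules. The third arm, which is the comparator in the main objective, receives no such training by allocation. Randomisation does not balance a difference that arises from the treatment itself, and blinding the assessor does not remove it. The Discussion relies on equal therapist time and on the eligibility criteria. These address placebo exposure and patients' other impairments, not familiarity with the task.

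At stake is the interpretation of CaCT versus AP and of ACT versus AP. Faster pressing on a familiar kind of task would be read as better attention. The Sample size section then feeds the pilot's results into the planning of the follow-up trial, so any practice component would be carried into it.

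The Go/No-Go description is a second, separate weakness in the same outcome section. It names a construct (suppression) and a score (reactions to targets) that do not correspond.

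**Working it through.** **1. Sample size and training dose.** The Sample size section gives 3 clinics × 20 = 60, which matches its stated total. With 1:1:1 allocation, 60 / 3 = 20 per arm. Assigned computer training is 4 weeks × 5 days × 30 min = 600 min = 10 hours in CaCT and in ACT, and 0 in AP. The plan gives no effect size, SD or power to reproduce.

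**2. TAP subtests set against the trained modules.**

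| TAP subtest | Module of the same name in CaCT/ACT | Shares computer test setting |
|---|---|---|
| Alertness (two conditions) | Yes | Yes |
| Divided attention | Yes (Training 1 and 2) | Yes |
| Go/No-Go | No | Yes |
| Incompatibility | No | Yes |

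By name, 2 of 4 subtests are matched. Counting the two Alertness conditions separately, this is 3 of at least 5 scores. The paper-based T2B and TMT share neither the module names nor the computer.

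**3. Contrasts affected.** CaCT versus AP and ACT versus AP each compare an arm assigned this training with one that is not. ACT versus CaCT is unaffected, because both arms receive it.

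**4. Illustration of size.** Let d be a purely task-specific gain in SD units, with no true difference in attention. The documents give no value, so d = 0.2, 0.3 and 0.5 are assumptions. For a two-sample t test with n = 20 per arm, df = 38 and noncentrality d × √(n/2) = d × √10, i.e. 0.632, 0.949 and 1.581. The probability of a significant result is P(|T| > critical value), where T is noncentral t:

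| Two-sided level | Critical value | d = 0 | d = 0.2 | d = 0.3 | d = 0.5 |
|---|---|---|---|---|---|
| 0.05, unadjusted | 2.024 | 5% | 9.5% | 15.2% | 33.8% |
| 0.05/3 (assumed: three pairwise tests) | 2.505 | 1.7% | 3.8% | 7.0% | 19.2% |
| 0.05/5 (assumed: five TAP scores) | 2.712 | 1% | 2.5% | 4.8% | 14.4% |

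The Statistical methods section plans ANOVA or Kruskal-Wallis with Bonferroni for multiple outcomes but does not give the divisor. The lower rows are therefore nearer to the plan than the first, and none is the planned procedure exactly. The multiplicity correction lowers the error rate but leaves the estimate shifted by the full d, whatever the sample size.

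**5. Go/No-Go.** Take two patients who respond equally fast. One presses only at the two target patterns; the other presses at all five.

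| | Correct reactions to targets | Reaction time | False reactions to non-targets |
|---|---|---|---|
| Presses at the 2 targets only | all | fast | none |
| Presses at all 5 patterns | all | fast | at all 3 non-target patterns |

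The two scores that the section describes cannot separate these patients. Only the third column does, and the section does not name it.

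**The case against.** **A reader might infer that the trained tasks are near copies of the TAP.** The documents do not show this. Task content is left to the developer's site, and the protocol assigns RehaCom Alertness to selectivity but TAP Alertness to basic attention. The overlap shown is one of name, medium and response.

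**A reader might infer that practice and attention gain cannot be told apart at all.** This is also too strong. T2B and TMT are paper tests of attention-related performance, already among the outcomes for all arms, and they allow an indirect check. Go/No-Go and Incompatibility help less: they use the same computer battery, so familiarity with the device could reach them too.

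**Only two arms practise.** This holds by allocation only. The Conventional therapy section permits CaCT in any arm where it is part of the clinic's usual care, and has it documented. That may dilute the imbalance but does not remove it.

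**The error rates rest on an assumed shift.** This is correct, and the unadjusted row omits the planned Bonferroni correction. The rates illustrate the mechanism; they do not estimate what will happen.

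**The choice may be deliberate in an exploratory pilot.** CaCT targets intensity, selectivity and divided attention, and those are the functions to be assessed. This stands as a reason to keep the TAP as primary and not to make its conclusion depend on secondary measures agreeing. It does not remove the need to say what a gain limited to trained-type subtests means.

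**Go/No-Go is summarised in one sentence.** The standardised test may well record errors, and the article does not say that false reactions go unrecorded. Even so, the score that the text ties to suppression is one that cannot show it. This point is separate from practice and does not make the practice problem larger.

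**Conclusion.** The concern holds in a limited form. An advantage of CaCT or ACT over AP on the TAP may partly reflect task and device practice, because the primary test shares its computer medium, its button response and two named functions with 10 hours of training assigned to those arms and not to AP. The protocol article does not mention this. The size is unknown. Under an assumed carry-over of 0.2 to 0.5 SD, 20 per arm and no true difference, the chance of a significant CaCT-versus-AP result runs from 9.5% to 33.8% unadjusted, and from 2.5% to 14.4% with an assumed divisor of 5. In either case the estimate passed to the follow-up trial is shifted by the whole carry-over. The documents support neither identical tasks nor an uninterpretable main comparison.

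The Go/No-Go point needs no assumption about carry-over. As described, neither correct reactions to targets nor reaction time can show suppression of an inappropriate reaction.

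**What to change.** 1. Before unblinding, label the TAP subtests as name-matched (Alertness, Divided attention) or unmatched (Go/No-Go, Incompatibility). Report the CaCT-versus-AP and ACT-versus-AP estimates separately for each set, beside the paper-based T2B and TMT-A. TMT-A is preferable to TMT-B here because the Chinese version of TMT-B uses a different task (Digit Symbol Coding). Describe a gain confined to the matched subtests as improvement on trained-type tasks. No formal gate on the secondary measures is needed.
2. Score Go/No-Go on false reactions to non-targets, with reaction time and correct reactions as supporting measures.

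The cost is revised wording in the outcome and interpretation sections and slightly more reporting. No test or visit is added. The downside is that a gain seen only on matched subtests would support a narrower claim.

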### Secondary outcome measures

#### Trail Making Test (TMT)

The TMT is a popular neuropsychological test and is included in most cognitive test batteries [30]. The TMT provides information on visual search, scanning, speed of processing, mental flexibility, and executive functions. The TMT consists of two parts. TMT-A requires an individual to draw lines sequentially connecting 25 encircled numbers distributed on a sheet of paper. Task requirements are similar for TMT-B except the person must alternate between numbers and letters (e.g. 1, A, 2, B, 3, C, etc.). The score on each part represents the amount of time required to complete the task(s). The Chinese version of the TMT-B uses Digit Symbol Coding [31]. The reliability and validity of the TMT test has previously been shown [32, 33].

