**Methods/Design:**

An international multicentre, single-blinded, randomised controlled pilot trial will be conducted. In a 1:1:1 ratio, 60 inpatients with post-stroke cognitive dysfunction will be randomly allocated into either the acupuncture group, the computer-assisted cognitive training group, or the ACoTrain group in addition to their individual rehabilitation programme. The intervention period of this pilot trial will last 4 weeks (30 minutes per day, 5 days per week, Monday to Friday). The primary outcome is the test battery for attentional performance. The secondary outcomes include the Trail Making Test, Test des Deux Barrages, National Institute of Health Stroke Scale, and Modified Barthel Index for assessment of daily life competence, and the EuroQol Questionnaire for health-related quality of life.

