### Participant and recruitment

The participants will be recruited from three inpatient stroke rehabilitation units from (1) Fujian University of Traditional Chinese Medicine Subsidiary Rehabilitation Hospital; (2) m&i-Fachklinik Herzogenaurach; and (3) Reha Rheinfelden. Patients will be identified and recruited via the clinic’s database according to diagnosis and medical referral. Respective medical personnel will be asked to invite patients from the population under investigation. Patients who express a general interest in taking part in the study will meet with one of the study personnel to receive all necessary information in oral and written form. After a 24-hour consideration period, the patient will be reapproached by the investigator to resolve any uncertainties and to be invited to sign informed consent after an assessment of eligibility criteria. After baseline assessment, patients who meet the inclusion criteria will be randomly allocated to one of the three study groups. A CONSORT diagram of participant recruitment is shown in Table 1.

**Table 1 Tab1:** Trial processes chart

Study periods	Admission	1^st^ *c*ontact	2^nd^ *c*ontact	Eligibility	Assessment	Treatment	Follow-up
Visit Duration	Week 1	Week 1	Week 1	Week 1	Week 1	Week 2–5	Week 6
		10 min	10 min	1 hour	3 hours	(4 × 5 × 30 min)	3 hours
Time	−7d	−6d	−5d	−4d	−4-0d	−2d	27d
Admission	x						
Medical examination	x						
Patient information		x			x		
Consultation			x				
Informed consent				x			
Demographics				x			
Medical history				x			
In-/exclusion Criteria				x			
Randomisation						x	
Administer study						x	
Primary variables					x		x
Secondary variables					x		x
Concomitant therapy						x	
Adverse events						x	x

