#### National Institute of Health Stroke Scale (NIH-SS)

The NIH-SS is a standardised assessment of neurological functions in the acute phase of stroke [34]. It is generally used to quantify improvement of the patient’s neurological impairments on 15 items in 11 areas of different neurological status. The administering medical doctor observes the patient and rates each item on an ordinal scale with three to five levels. A maximum of 42 points can be achieved, which would correspond to severe neurological impairment. The NIH-SS will be recorded once to allow classification and description of the severity of stroke of the included patients. It is generally provided by the referring hospital. If not, the treating neurologist may reconstruct it retrospectively [35].

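### TMT-B is a different task at the Chinese centre although pooling is claimed for all data, and the NIH-SS is listed as a secondary outcome but recorded only once

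*Protocol article*

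**What the plan says.** **TMT-B.** The section on the Trail Making Test describes part B as alternating between numbers and letters and scores each part by completion time. It then states: "The Chinese version of the TMT-B uses Digit Symbol Coding". The Discussion says that "the usage of standardised and cross-culturally adapted assessments allows comparison and pooling of all study data coming from different trial centres", and its later paragraph on cultural differences adds that the assessments measure one construct irrespective of culture, education or language. Neither statement makes an exception for TMT-B.

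**NIH-SS.** The abstract (Methods/Design) says: "The secondary outcomes include the Trail Making Test, Test des Deux Barrages, National Institute of Health Stroke Scale, and Modified Barthel Index". The scale also has its own entry under Secondary outcome measures. The Outcome assessment section sets the timing: "Outcomes will be measured once before intervention (T0) and once after intervention (T1, at 4 weeks". Table 1, under Participant and recruitment, marks the row "Secondary variables" at the baseline assessment and again at follow-up. The NIH-SS section says otherwise: "The NIH-SS will be recorded once to allow classification and description of the severity of stroke of the included patients". On its source it says: "It is generally provided by the referring hospital". Failing that, the treating neurologist may reconstruct it afterwards.

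**Analysis.** The Statistical methods section plans ANOVA or Kruskal-Wallis for the outcome measures, a Bonferroni adjustment for multiple outcomes, and descriptive statistics by group for baseline values. It does not say whether scores at T1 or changes from T0 are compared.

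**The concern.** A pooled result needs one instrument, or at least instruments put on a common scale. The article names a substitution at one of its three centres and still claims that everything can be pooled. If raw values were combined under the single label TMT-B, the mean, the spread and the arm contrast would come from a mixture of two tests. The Sample size section intends to plan the full-scale trial from these results, so a standard deviation taken from such a mixture could be carried into that calculation if TMT-B is used for it.

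The NIH-SS problem is one of status. A single value that comes from before the study treatment describes who was enrolled. It cannot respond to treatment, so it should not stand among the outcomes by which the arms are compared.

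**Working it through.** **Inputs**
- Recruitment: 20 patients at each of three clinics, 60 in total (Sample size).
- Centres: one in China, one in Switzerland, one in Germany (Study design and setting).
- Allocation: 1:1:1 (abstract, Methods/Design), with a separate randomisation list for each centre (Randomization and blinding).
- Outcome occasions: two, T0 and T1 (Outcome assessment; Table 1).
- NIH-SS occasions: one (NIH-SS section).

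**Step 1. The plan's own total.** 3 × 20 = 60, as stated. No effect size, standard deviation or power is given, so there is no power figure to reproduce.

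**Step 2. Patients with another test under the TMT-B label.** One centre of three: 20/60 = 33%. Patients who share TMT-B as defined: 60 − 20 = 40, or about 40/3 ≈ 13 per arm, against 60/3 = 20 per arm for an outcome common to all centres. Nothing in the article suggests that TMT-A differs between centres.

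**Step 3. What mixing does, and what it does not do.** Suppose, generously, that the Chinese score is a linear version of the TMT-B score Y, namely a + bY. Here a is a shift in location and b carries the unit, the spread and, through its sign, the direction of scoring.
- Single-time score: a + bY. Both a and b enter the pooled data.
- Change score: (a + bY₁) − (a + bY₀) = b(Y₁ − Y₀). The shift a cancels and b remains.
- Score standardised within centre: subtracting the centre mean removes a, dividing by the centre SD removes the size of b, and aligning direction removes its sign.

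The article gives neither a nor b and does not say whether T1 or change scores are tested. The direction of the problem is therefore clear, but its size cannot be computed. If the analysis uses change scores, a difference in location alone does no harm, while a difference in unit, spread or direction still does.

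**Step 4. NIH-SS passages side by side.**

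| Place | Status or timing |
|---|---|
| Abstract, Methods/Design | Secondary outcome |
| Heading of the NIH-SS section | Under Secondary outcome measures |
| Outcome assessment | Outcomes at T0 and T1 |
| Table 1 | Secondary variables at baseline and follow-up |
| NIH-SS section, text | Once, descriptive, from the referring hospital or reconstructed |

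The first four rows together require two values per patient and the last allows one. A change needs two, so it can be formed for 0 of 60 patients. The sources named in the last row also place the value before study treatment, so it cannot serve as a T1 score either.

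**The case against.** The strongest reply has four parts.

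**Pooling is a Discussion statement, not an analysis rule.** The Statistical methods section prescribes no raw pooled TMT-B test. Centre terms and standardisation are commonly left to an analysis plan, which is not shown. The abstract also speaks of assessments validated for each region, so regional versions are acknowledged. This stands as far as it goes: a missing centre term is no fault here. But the claim that pooling holds for all study data is made in this article, and the article's own instrument description contradicts it.

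**The scoring may be the same.** The only scoring rule given is completion time. If it also covers the Chinese version, unit and direction agree. That is possible, and for this reason no reversal of direction should be asserted. The task would still differ. If the Chinese centre in fact uses an adapted trail-making task, the sentence is misworded and needs correcting.

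**The damage can be overstated.** A reader might infer a definite loss of precision, a definite dilution of the effect, or a pooled result that is uninterpretable whatever is done. The documents support none of these. Any such figure needs an assumed shift or scoring direction that they do not give, and a location shift cancels in change scores. Because each centre has its own randomisation list, the comparison of arms within a centre stays valid whichever test that centre uses.

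**No test of the NIH-SS between arms is spelled out.** A reader might infer that it uses up a share of the Bonferroni correction. Its section gives a descriptive purpose, and baseline values are to be described only, so that cost is not established. What remains is that a baseline descriptor is labelled as an outcome, in conflict with the measurement schedule.

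**Conclusion.** Both parts hold, at moderate weight.

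- **TMT-B:** one third of the planned patients (20 of 60) would have a value from a different task, which contradicts the claim of one construct and of pooling for all data. This rests on the plain reading of the Trail Making Test section and on the recruitment target of 20 per clinic. How far a raw pooled result would be distorted is unknown.
- **NIH-SS:** the contradiction between one recording and two scheduled occasions is certain on the text. As described, the scale gives no before-after change and cannot show a treatment effect.

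A reader might take this as a flaw that undermines the trial. It does not: one part of one secondary test and one severity scale are affected, the study is an explorative pilot, and the primary outcome (TAP) and TMT-A are untouched.

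**What to change.** **TMT**
1. Pool TMT-A over all three centres.
2. Analyse TMT-B in the two centres that share it (n = 40), and report Digit Symbol Coding from the Chinese centre separately, under its own name and with its scoring stated.
3. If one combined figure is wanted, use only scores standardised within centre and aligned in direction, with centre in the model.
4. Exclude TMT-B from the statement that all data can be pooled.

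**NIH-SS**
1. Move it from the secondary outcomes to the baseline characteristics, in the abstract and in the section structure.
2. Leave it out of the outcomes that are tested and counted in the Bonferroni correction.
3. Using it as a covariate or as a predictor in imputation is optional; nothing shown here requires it.

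**Cost.** Wording and analysis only, with no new data. The TMT-B estimate would rest on 40 patients, about 13 per arm, and Digit Symbol Coding on 20, about 7 per arm (20/3), so both will be imprecise. A combined standardised figure keeps all 60, but assumes that the two tasks respond comparably in SD units.
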